## Abstract

Acquiring movement skills is crucial across the lifespan, supporting an individual’s participation in sports and physical activities. Errorless motor learning, which promotes success during practice, has been shown to be effective for acquiring or reacquiring (e.g., following injury/disease) movement skills. This research explores the underlying processes of errorless motor learning in children and older adults. We will investigate two distinct processes associated with motor learning: (i) cognitive processing measured by movement variability and prefrontal cortex (PFC) activity and (ii) affective processing measured by perceived competence. We will recruit two participant groups—children, and older adults—who will practice a novel throwing task in either a condition where errors are minimized or a condition where errors freely occur. We will measure task performance, movement variability, perceived competence, and PFC activity before, during, and after practice. We will control for individual cognitive abilities (processing speed and executive function) and use hierarchical linear mixed models to compare the variables between the practice conditions and to verify whether the cognitive and affective processes influence outcomes following practice. The findings are expected to contribute to our understanding of skills acquisition across the lifespan and help facilitate the (re)acquisition of motor skills by children and older adults through programs provided by physiotherapists, coaches, teachers, and health professionals. This study has been registered in the Open Science Framework Registries (https://doi.org/10.17605/OSF.IO/YTERV).

## Introduction

1

Across the lifespan, movement skills allow us to engage with our immediate environments, engage in sports and physical activity, and maintain independent performance of daily functions. Our ability to learn and perform movement skills evolves from childhood to late adulthood (Leversen et al., 2012), and strategies to promote the acquisition of movement skills need to adapt to lifespan changes. Errorless motor learning is a strategy that has been shown to benefit children and older adults (e.g., Maxwell et al., 2017; Chauvel et al., 2012), but the effectiveness of errorless motor learning can be optimized by understanding how people of different ages learn and perform movement skills. In this study, we examine the cognitive and affective processes that occur during errorless motor learning in children and older adults.

### Motor learning

1.1

Motor learning consists of internal processes associated with practice or experience that lead to relatively permanent changes in movement skill proficiency (Schmidt and Lee, 2020). Adams (1971) described motor learning as a problem-solving process in which movement errors are solved using cognitive resources. Thus, a cognitive process has long been considered an underlying factor in acquiring movement skills. For instance, in their seminal work, Fitts and Posner (1967) described cognitive, associative and autonomous stages of learning. During the initial cognitive stage, learners discover and use rule-based knowledge to monitor and control their movements. Movement strategies are refined during the associative stage, and subsequent performance has little reliance on rule-based knowledge during the autonomous stage. The cognitive stage has been suggested to require working memory resources to support the processing, storage, and manipulation of incoming sensory information (Maxwell et al., 2003).

With this understanding, movement skills are considered to be acquirable explicitly or implicitly (Masters, 1992). Movement skills that are learned explicitly are accompanied by the accumulation of declarative knowledge (i.e., rules, mechanics of movement) that is used to support motor performance (Maxwell et al., 2003). Movements that are learned implicitly do not necessarily require increased knowledge of rules and mechanisms to support performance, despite learners being aware that they are learning the movement(s) (Masters, 1992). For example, Maxwell et al. (2001) reported that implicit learners verbalized fewer rules related to motor performance than explicit learners did. Children have also been shown to accumulate more knowledge during explicit learning conditions (van Abswoude et al., 2020). With respect to the stages of motor learning, the cognitive phase appears particularly crucial in explicit but not in implicit motor learning. Age and intelligence (e.g., IQ), which are related to working memory capacity, have also been identified as individual factors that affect explicit, but not implicit, motor learning (Steenbergen et al., 2010).

### Errorless motor learning

1.2

One approach to promote implicit motor learning is to minimize errors during practice, i.e., errorless motor learning. When learners experience practice errors, they seek—and test—alternative movement solutions, form rules to support movement performance, and consequently utilize working memory resources (Maxwell et al., 2001). This typically promotes explicit motor learning. In contrast, when learners experience fewer practice errors, they are less likely to utilize working memory resources to explicitly seek—and test—alternative movement solutions (Capio and Eguia, 2021). For instance, young adults learning a golf putting task actively modified their movements following unsuccessful performance, suggesting that experiencing practice errors involved hypothesis testing behaviors (Poolton et al., 2005). More recently, Banihosseini et al. (2025) reported that motor performance was unaffected by mental fatigue during errorless motor learning showing limited reliance on working memory.

Errorless motor learning promotes implicit learning by manipulating constraints, such as task difficulty. In the early stage of learning, movement training might begin with an easy task during which learners experience few practice errors (Capio and Eguia, 2021). Poolton et al. (2005) reported that early experiences of success during practice develop movement skills that tend to be independent of working memory, which is consistent with implicit motor learning. Early success in practice is critically important, and machine learning methods have shown that initial performance in skill learning strongly predicts final task performance (Abeles et al., 2023). Indeed, errorless motor learning has been consistently shown to improve movement outcomes, including gross motor skills (Capio et al., 2017) and novel sporting skills (Maxwell et al., 2017).

While freely occurring practice errors hamper performance during learning, other research has shown that performance outcomes subsequently improve significantly (Lee et al., 2016), which suggests that errorless motor learning may not necessarily be advantageous. However, a key advantage associated with errorless motor learning is that learners can manage multiple tasks while displaying effective movement performance after the learning phase. This benefit has been shown in studies of children (Capio et al., 2013a, 2013b) and older adults (Chauvel et al., 2012) and may be explained by the relative independence of errorless learning from working memory resources. For instance, children with low working memory capacity showed enhanced learning when they made fewer errors during practice (van Abswoude et al., 2015). With less reliance on cognitive resources, the apparent defining advantage of errorless motor learning lies in the ability to rely on movement skills when individuals need to engage with competing attentional demands (e.g., children in playgrounds who are socializing with others and older adults who are minding environmental constraints during exercise).

Early success in practice may also lead to advantages in motivation and self-efficacy (Lee et al., 2016). In the Optimizing Performance Through Intrinsic Motivation and Attention for Learning (OPTIMAL) theory proposed by Wulf and Lewthwaite (2016), early experiences of success increase expectancy and perceived competence, which are key drivers of affective modulation, such as increased self-confidence. As shown by Chiviacowsky et al. (2012), perceived competence and self-efficacy are associated with more effective motor learning among children. Iwatsuki and Regis (2021) also reported that among young adults who performed a throwing task with their nondominant arm, fewer errors during practice was associated with greater perceived competence and superior movement performance compared with more errors during practice. It is generally considered that motivation drives individuals to direct effort and engage with the task, thus optimizing learning (Manohar et al., 2015; Summerside et al., 2018). For instance, Capio et al. (2013a) reported that children with intellectual disability who practiced with fewer errors displayed a greater tendency to use their gross motor skills during free play than did those who practiced with more errors. Moreover, when fewer errors are associated with rewards, training has been shown to induce long-term retention of skills (Abe et al., 2011) through memory consolidation, which is evident in neural mechanisms involving dopamine pathways and the primary motor area in the brain (Zhao et al., 2024). Studies of animal models have also shown that sensorimotor cortical neuron activity concurrently represents movement performance and anticipation of rewards, suggesting neural mechanisms associated with affective modulation (Ramakrishnan et al., 2017).

### Underlying processes of errorless motor learning

1.3

The potential underlying processes of errorless motor learning have yet to be empirically tested. Owing to the implicit nature of errorless motor learning, it has been frequently suggested that it requires relatively low cognitive demands, as proposed by Maxwell et al. (2003). For example, despite cognitive impairments, children with intellectual disability who learn via errorless motor learning display improvements in gross motor skills and the ability to perform multiple tasks (Capio et al., 2013a). In other research involving adults without impairments, learning a novel locomotor task (i.e., split-belt treadmill walking) with few errors was found to be less dependent on cognitive resources—on the basis of reaction time to a secondary cognitive task—compared to when greater movement errors were generated (Sawers et al., 2013). Earlier studies demonstrated relatively greater conscious control by learners when they experienced more errors, as evidenced by increased coactivation of brain regions associated with movement processing (Zhu et al., 2011). As processing errors to adjust movement planning requires significant cognitive resources, the efficacy of errorless motor learning could be explained by the relatively reduced cognitive requirements. However, no study thus far has offered direct evidence that such cognitive factors differentiate errorless motor learning from learning with copious amounts of practice errors during the process of skill acquisition.

A behavioral representation of the cognitive processes during motor learning is the variability of movement, or trial–to–trial deviations of movement kinematics, which become evident when task difficulties vary (Lajoie and Franks, 1997). Movement variability may be considered to represent real-time cognitive engagement that is closely coupled with motor performance. Learners display relatively low movement variability when movement tasks demand high accuracy. A study of young adults engaged in a throwing task revealed greater movement variability during errorless motor learning than during errorful motor learning, and movement variability was negatively associated with conscious control (van Ginneken et al., 2018). These findings support the proposition that errorless motor learning is associated with relatively lower conscious control.

Cognitive processes during motor learning can also be assessed through direct measures of brain activity (Nishiyori et al., 2016). However, direct measures of brain activity [e.g., electroencephalography (EEG); functional magnetic resonance imaging (fMRI)] have been limited by practical and technological constraints. For example, due to noise generated by large, dynamic body movements, the use of EEG has been limited to studies of fine motor skills (e.g., Zhu et al., 2011). Functional near-infrared spectroscopy (fNIRS), which enables monitoring of brain activity, as reflected by changes in cortical oxygenation, has been suggested to be capable of overcoming the limitations associated with large body movements (Ferrari and Quaresima, 2012). Prefrontal cortex (PFC) activity, which is considered a representation of working memory engagement (Riley and Constantinidis, 2016), may be measured via fNIRS during motor learning activity. Studies have shown that fNIRS is suitable for naturalistic and ecologically valid conditions (Ayaz et al., 2019) where dynamic motor tasks are involved (e.g., walking on a treadmill, Koenraadt et al., 2014).

Affective processes during motor learning could also explain the relative efficacy of errorless motor learning. Success during practice has been conceptualized as a mediator of the positive effect of perceived motor competence on subsequent motor performance (Li et al., 2020). Errorless motor learners could be encouraged to engage in the motor task further (i.e., more practice at their own volition), leading to skill improvements (Capio et al., 2013a). It is, therefore, possible that affective states differentiate errorless motor learning from practice conditions with freely occurring errors, where participants’ motivation for practice is enhanced by experiences of success, but this has yet to be directly examined.

Affective states in motor learning research have been measured using questionnaires. Levac and colleagues (Levac et al., 2017) used the validated Intrinsic Motivation Inventory (IMI (Ryan, 1982) to measure intrinsic motivation in a study that examined the frequency of errors and autonomy in motor learning. The IMI subscales, which consist of interest/enjoyment, perceived competence, effort, value/usefulness, pressure and tension, and perceived choice, have also been used selectively in motor learning studies that included older adults (e.g., Iwatsuki and Regis, 2021). The IMI has also been adapted to measure the perceived competence of children (e.g., Ávila et al., 2012).

### Current study and objectives

1.4

To date, there has been no deliberate examination of the cognitive and affective processes related to errorless motor learning. From a theoretical point of view, understanding these associated processes contributes to our knowledge of skill acquisition in relation to practice errors. From a practical perspective, an understanding of associated cognitive and affective processes can guide how practice should be structured to promote more efficient learning of movement skills; in this study, specifically for children and older adults. Movement-related concerns vary across the lifespan, primarily with respect to independent and effective performance of social and occupational roles (e.g., attending school, maintaining independent mobility). Understanding the variance (or invariance) of the cognitive and affective processes of errorless motor learning in childhood and late adulthood is especially important given the need to support the design of developmentally appropriate programs during the lifespan periods when people crucially need to acquire (i.e., rapid neurodevelopment in children) or maintain (i.e., age-associated decline in older adults) the ability to move well. This current study is also complemented by related research involving young adults (see project registration at https://doi.org/10.17605/OSF.IO/ZUREH), which contributes to evidence generation across the lifespan.

This study aims to examine the cognitive and affective processes associated with errorless motor learning. We investigate whether (i) cognitive processing is reduced during errorless motor learning given its implicit nature and whether (ii) the affective state is enhanced following early experiences of success. The study involves participants in the lifespan tail ends who will participate in an experiment that contrasts errorless with errorful motor learning. We will measure task performance along with behavioral indicators of cognitive (i.e., movement variability) and affective (i.e., perceived competence) states before, during, and after the practice of a functional motor task. In addition, we will use fNIRS as a direct measure of blood oxygenation changes in the PFC, which represents working memory activity (Riley and Constantinidis, 2016).

We hypothesize that the changes during the learning phase significantly differ between errorless and errorful learning conditions for (i) movement variability, (ii) perceived competence, and (iii) PFC activity. We further hypothesize that the changes across the same variables and task performance significantly differ from before to after practice between errorless and errorful learning conditions. Finally, we will test whether the changes in task performance from before to after practice are moderated by movement variability, perceived competence, or PFC activity.

## Methods and analysis

2

This study was reviewed and approved by the research ethics committee of the primary affiliated university of the first author (Ref. no. HE-RGC2024/NHS10). All the procedures are in compliance with the principles of the Declaration of Helsinki. Research staff will obtain written consent for participation from older adults and parents of children, while verbal assent will be obtained from the children. This study was registered in the Open Science Framework Registries (https://doi.org/10.17605/OSF.IO/YTERV). Based on the planned timeline, data gathering commenced in August 2025 and is expected to end by June 2026.

### Participants and eligibility criteria

2.1

This study protocol was developed and reported following the updated Standard Protocol Items: Recommendations for Interventional Trials (SPIRIT) guidelines (Chan et al., 2025). The research consists of two experiments, which follow the same design but with adaptations to suit the developmental requirements of children and older adults.

Corresponding to the two experiments, the following participant groups will be formed: (i) children aged 6 to 8 years and (ii) older adults aged 60 years and older. For both participant groups, the inclusion criteria are as follows: (i) normal or corrected-to-normal visual acuity and (ii) no diagnosed neurodevelopmental, medical or orthopedic conditions that constrain the stability and mobility of the upper limb or trunk. For cognitive screening, children should not require support for special educational needs; older adults should score ≥ 24 on the Chinese version of the Mini–Mental State Examination. Owing to the task, those who are ambidextrous will also be excluded (see Procedures below for the task). We acknowledge that these exclusion criteria allow us to control the experimental conditions but limit the generalizability to populations without cognitive or physical impairments.

Using GPower 3.1.9.7 and assuming an analysis based on hierarchical linear regression, a sample size of 46 participants for each age group is needed to determine the effects of errorless and errorful learning conditions on movement performance. The parameters include an effect size of 0.23 based on improvement in task performance (i.e., number of successful hits) that differentiated errorless and errorful conditions among young adults that followed a similar protocol (Capio and Eguia, 2025), 80% power, and an alpha of 0.05. Because the procedures will take place over two sessions and fNIRS procedures may be uncomfortable and challenging to some, we will aim to recruit 52 participants per age group (i.e., ~10% additional) to mitigate the potential impact of sample attrition and/or data loss.

Recruitment of participants will be conducted by research assistants through public announcements on the social media pages of the university and nearby communities. Interested participants will be able to contact the research team directly through online messaging (i.e., WhatsApp) and will be scheduled for screening and experiment participation. Informed consent and verbal assent (for children) will be obtained by the research assistants. Within each age group, participants will be randomly assigned in equal numbers by sex to either the errorless (EL) or errorful (EF) group via stratified block randomization. The random allocation block sequence will be computer-generated by research staff not involved in participant recruitment or assignment.

Participants will be informed only about the procedures and requirements of the group to which they were allocated and without knowledge that an alternative condition exists. Due to the nature of the study procedures, research staff will be aware of group assignment for protocol implementation. Thus, while participant blinding is implemented to the extent possible, research staff cannot be blinded, and this limitation is acknowledged as inherent to the study design.

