Each experiment will be conducted over 2 days with 1 day in between, and it will consist of a pretest, a learning phase, and a posttest, as illustrated in Figure 1. The learning phase consists of two practice sessions. In each session, participants will perform 10 blocks of 15 practice trials per block, with two-minute rest periods between blocks (i.e., 150 practice trials per session). The occurrence of practice errors can be influenced by manipulation of task constraints, such as target size (Capio et al., 2013b; van Ginneken et al., 2018). As such, the practice conditions for the EL group consists of a circular target with a 100 cm radius which will be used in the first two blocks of practice; the target radius progressively decreases by 10 cm (i.e., 100 cm, 90 cm, 80 cm… 20 cm, 10 cm) after every two blocks. Thus, the target radius in the first practice session decreases from 100 cm to 60 cm, and in the second practice session, it decreases from 50 cm to 10 cm. The practice condition for the EF group consists of a circular target with a 10 cm radius which will be used throughout all practice sessions.

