**Figure 1 fig1:**
[figure not shown]
Schematic diagram of the study procedures.

In the test phases (i.e., pretest and posttest), the target consists of 10 concentric circles with radii that increase from 10 cm to 100 cm (in increments of 10 cm). Hitting the innermost ring corresponds to the highest possible score per trial (i.e., 100 points). The score is reduced by 10 points for each ring that is incrementally more distant from the center; a score of zero is given for throws that fail to hit any part of the target. A similar task has been used in previous motor learning studies (Chiviacowsky et al., 2012). See Figure 2 for an illustration.

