### Outcome measures

2.3

The outcome measures consist of task performance, movement variability, perceived competence, and PFC activity. Covariate measures include cognitive processing speed and executive function capacity.

Task performance during the learning phase is measured by the number of successful hits on the target in each block. Task performance during the test phase is measured by accuracy scores. Task performance scores will be measured in real time by two independent observers and verified *post hoc* using video recordings of the target. The range of scores for successful hits during learning is 0–15 per block, and the ranges for accuracy during the tests are 0–100 per trial and 0–1000 for each test (Capio and Eguia, 2025).

Movement variability will be calculated using the coefficient of variation (CV) of the joint angles and joint velocity. CV is defined as the standard deviation divided by the mean (expressed as a percentage) and provides a normalized measure of how consistently joint kinematics are maintained across repeated movements (Mukherjee and Yentes, 2018). Movement kinematics will be generated using the Noraxon MyoMOTION system (Noraxon Inc., United States), which uses inertial measurement units (IMUs) to track the three-dimensional angular changes in the upper limb used for throwing. This instrument has been shown to provide valid estimates of joint kinematics (Heuvelmans et al., 2025). Four IMUs will be positioned on the (i) dorsum of the hand, (ii) dorsal side of the distal half of the forearm, (iii) lateral side of the middle third of the upper arm, and (iv) over the spine of the upper thoracic region.

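### Blinding of research staff is ruled out altogether, yet test-phase accuracy could be scored by someone unaware of the arm, from video that is already planned

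*Protocol article*

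**What the plan says.** All references are to the protocol article.

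- **Section 2.1, on blinding.** Staff knowledge of the arm is explained by one need: "research staff will be aware of group assignment for protocol implementation". The conclusion drawn carries no exception: "research staff cannot be blinded, and this limitation is acknowledged as inherent to the study design".
- **Section 2.2, practice.** The arms practise on different targets. In the errorless arm "the target radius progressively decreases by 10 cm" after every two blocks, starting from 100 cm. The errorful arm has a "circular target with a 10 cm radius which will be used throughout all practice sessions".
- **Section 2.2, tests (text after Figure 1).** For pretest and posttest "the target consists of 10 concentric circles with radii that increase from 10 cm to 100 cm". No difference by arm is described.
- **Section 2.3, scoring.** "Task performance scores will be measured in real time by two independent observers and verified" afterwards "using video recordings of the target". Nothing is said about whether the observers or the person checking the video know the arm.
- **Section 2.6, data handling.** Task performance is entered by research staff as it is collected, and participants are linked to their data through codes.

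**The concern.** The conclusion on blinding is wider than the reason given for it. Someone has to know the arm to put up the right practice target. Nobody needs to know it to judge where a ball landed on a test target that is the same for everyone. By declaring blinding of staff impossible, the article closes off a safeguard that the design allows.

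What is at stake is the test-phase accuracy score. Section 1.4 hypothesises that task performance changes differently between conditions from before to after practice. Section 2.6 then tests whether the process variables moderate that change. Both rest on test-phase accuracy. If scorers know the arm and the hypothesis, close calls at a ring boundary can lean towards the expected result. A lean that differs between arms is bias, and more participants do not remove it.

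**Working it through.** The article gives no figure for observer error, so the check is mainly a comparison of its own statements. A short calculation on size follows.

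**1. Who is covered by the stated reason?** Running the protocol requires knowledge of the arm because the practice target differs (section 2.2). This covers staff who deliver practice. It also covers anyone counting learning-phase hits, since target size reveals the arm.

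**2. Does it cover test-phase scoring?** No. The pretest, the two retention tests and the transfer test use one ringed target. As described, a recording of that target does not show the arm.

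**3. Is the material for masked scoring already there?** Yes. Video of the target is to be used to verify the scores (section 2.3), and participant codes exist (section 2.6). There are 4 tests of 10 scored throws, so 40 throws per participant. With 52 recruits in each of 2 age groups, that is 2 × 52 × 40 = 4,160 throws at most. As section 2.3 is worded, their scores are already due to be verified.

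**4. Do the existing safeguards answer the point?** In part. Two observers and a video check catch random error and some bias. Independence between observers is not masking, however: two people who both know the arm can err in the same direction. Codes do not hide the arm from staff who ran that participant's session.

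**5. How large could the effect be?** One ring is worth 10 points and a test is scored out of 1000, so one misjudged ring moves the test score by 10/1000 = 1% of its range. The article gives neither the frequency of such errors nor an SD, so this cannot be turned into an effect size.

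As an illustration only, suppose there is no true effect and scoring shifts one arm by δ SD. For a two-sided 5% comparison of two means (normal approximation) with n per arm:

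Type I error = Φ(δ/SE − 1.96) + Φ(−δ/SE − 1.96), with SE = √(2/n).

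The values of n are 46/2 = 23 and 52/2 = 26, from section 2.1. The values of δ are assumed. For n = 23 and δ = 0.2, SE = 0.295 and δ/SE = 0.678, which gives Φ(−1.282) + Φ(−2.638) = 0.104.

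| δ (SD, assumed) | n = 23 per arm | n = 26 per arm |
|---|---|---|
| 0.1 | 6.3% | 6.5% |
| 0.2 | 10.4% | 11.1% |
| 0.3 | 17.4% | 19.1% |

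This is a simple two-means test, not the planned hierarchical model. It shows how a shared lean would act, not how large it is.

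**6. Does any planned number change?** No. Masked scoring leaves the 46 required and 52 recruited per age group as they are.

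**The case against.** The strongest reply is that the outcome is close to objective: where a throw lands on a ringed target, scored by two people and checked against a recording. A biased call would have to survive all of that. The authors also disclose the limitation openly, and section 2.2 mentions a written staff protocol, not shown here, that may say who reads the video. This stands as a reason to expect the bias to be small. It does not rescue the statement in section 2.1, which rules out masking altogether instead of leaving it unmentioned.

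A reader might infer more than the article supports:

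- **That a primary outcome is affected.** Section 2.3 lists four outcomes and ranks none. The sample size in section 2.1 rests on the number of successful hits, which section 2.3 defines as the learning-phase measure.
- **That test scoring will certainly be unmasked.** The article does not say who reads the video or what that person knows.
- **That arm-aware staff will discard kinematic or fNIRS trials or segments.** Section 2.6 refers to the vendors' standard procedures and describes no such step.
- **That the bias has a known size in points.** Any total needs an assumed number of boundary throws, all called in one direction and all surviving the checks. The article supports none of this.

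**Conclusion.** The point holds for test-phase accuracy scoring. The blanket statement in section 2.1 is too broad. Its reason covers practice delivery and learning-phase hit counts, and the article's own description shows that test throws can be scored without knowledge of the arm.

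The result is an avoidable risk of observer bias in the outcome behind the pre-to-post performance and moderation hypotheses. Its size is unknown, and the two observers and the video check already reduce it. The conclusion assumes that the test target is the same in both arms, as section 2.2 reads, and that clips can be cut to show that target alone. The change is worth making because it costs little; the point does not invalidate the design.

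**What to change.** - In section 2.1, limit the statement that staff cannot be blinded to practice delivery and learning-phase hit counts.
- In section 2.3, state that video verification of the pretest, retention and transfer throws is done from clips showing only the test target, labelled by participant code. The reader should be an existing team member who did not run that participant's sessions and has no access to the allocation.
- Use that score in the analysis and keep the live scores as a check.

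Section 2 says data gathering began in August 2025. Stored test videos can still be read this way, so the change can cover participants already tested. Delaying disclosure of the allocation until after the pretest could not, so the fix does not rely on it.

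The cost is some file relabelling, reassignment of a step already planned, and a short delay before final scores are available. Sample size and participant burden do not change.
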